# 1 Protocol Summary

## 1.1 Synopsis

| **Title:** | TranExamic Atomized for Pediatric post-Operative Tonsillectomy hemorrhage: A Pilot and Feasiblity Study |  |  |  |
| --- | --- | --- | --- | --- |
| **Study Description:** | This study starts as single site pilot study, randomized, double-blinded controlled trial for 12 patients. Then dependent on funding, the study will be a multi-center, randomized, double-blinded, placebo-controlled trial. It is a parallel arms pilot trial randomizing up to 30 patients. |  |  |  |
| **Objectives:** | \| Primary Objective: \| The primary objectives of this pilot study are:   1. Enroll 0.6 patient's/site/month with PTH and 2. Evaluate the ability to nebulize at least two doses of TXA to children with PTH and 3. Determine the indirect local and systematic concentrations of nebulized TXA in children 4. Adverse events will be assessed 30 +/- 5 days from randomization \| \| \| \| --- \| --- \| --- \| --- \| \| Secondary Objectives: \| The secondary objectives of this pilot study are:   1. Determine the number and rationale for PTH patients to return to the OR; and 2. Determine the number of blood transfusions and estimated blood loss and 3. Determine the recurrence of PTH after TXA, saline or return to the OR. \| \| \| \| Exploratory Objectives: \| \| Establish pain and anxiety inventory at 7 +/- 1 from randomization. \| | | |  |
| **Endpoints:** | \| Primary Endpoint: \| Enrollment after one year, % of nebulization administered to patient's enrolled, and collection of two blood samples from each participant. Adverse events will be assessed at 30 +/- 5 days from randomization. \| \| --- \| --- \| \| Secondary Endpoints: \| Collection of surveys on ENT decision to go to the OR, electronic health record data on blood transfusions and estimated blood loss, and if PTH recurrences within seven days of randomization. \| \| Exploratory Endpoints: \| Age-appropriate pain and anxiety states at 7 +/- 1 days after randomization. \| | | | |
| **Study Population:** | Children aged 2 to 17 years old that present with post-tonsillectomy hemorrhage (PTH), ENT clinicians, parents of the children enrolled and missed eligible. | |  |  |
| **Phase:** | 2 | |  |  |

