## 1.3 Schedule of Activities (SoA)

| **Procedure** | **Day 0-1***  **Enrollment** | **Day 7 +/- 1** | **Day 30 +/- 5 End of Study** |
| --- | --- | --- | --- |
| Screening and eligibility | X |  |  |
| Medical history | X |  |  |
| Consent | X |  |  |
| Demographics/baseline information | X |  |  |
| Concomitant medication review | X | X |  |
| ED/Hospital admission data collection** | X | X |  |
| Randomize to “use next box” | X |  |  |
| Administer study nebulization 1 | X |  |  |
| Administer study nebulization 2 | X |  |  |
| Administer study nebulization 3 | X |  |  |
| Surgical hemorrhage control (Y/N) | X | X |  |
| 1st TXA Level (last neb up to 60 mins) | X |  |  |
| 2nd TXA Level (60 mins to 8 hours) *** | X |  |  |
| ENT OR decision survey | X |  |  |
| Process, freeze, store, and ship samples | X |  |  |
| Age-appropriate Pain Scale |  | X |  |
| Parents and Children (Promis Anxiety Scale 8a) |  | X |  |
| Adverse and serious adverse events | X | X | X |

*Randomization to 24 hours

**Should include the following, if collected per standard of care: vital signs (including height and weight), physical exam, ENT upper airway exam, lab data collection (coagulation labs, other routine lab tests), OR use, ENT exam & findings as relating to OR use (e.g., photo of tonsillar bed), blood product usage, final hospital disposition. At seven days, further, evaluate if participants had been readmitted for bleeding after an intervention.

***Time points must be separated by 60 to 90 minutes.

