# 3 Objectives and Endpoints

| OBJECTIVES | ENDPOINTS | JUSTIFICATION FOR ENDPOINTS |
| --- | --- | --- |
| Primary | | |
| Evaluate the feasibility to enroll 0.6 patients/site/month  Nebulize at least two of three doses of TXA to children with PTH.  Determine the local and systematic concentrations of nebulized TXA in children  Determine incidence of adverse and serious adverse events | Enrollment after one year and % of nebulization’s. Go/no-go threshold is 0.6 patients per site per month for a total of 22 patients. Time and success to obtain consent will establish need for exception for informed consent (EFIC).    The goal is >90% of patients will receive at least two of three planned nebulization of TXA.  Collection of two blood samples from each participant. This will verify a pulmonary physiological-based PK model (PBPK) (i.e., nasal cavity, pharynx, and lung) that indirectly predicts the oropharyngeal and systematic concentration of nebulized TXA.  A phone call or email will be placed to participants at 30 +/- 5 days. | The overall incidence of PTH is 5%, yet numbers per site may be very different. Assessment and consent will optimize site selection, recruitment process, and the plan the main trial.    The establishment of a pragmatic protocol design will help design a large trial.  Limited data on nebulized TXA systematic absorption. Topical PK studies of TXA document a significant reduction in systematic levels but the same hemostasis effect.  Safety Evaluation as recommended by the FDA. |
| Secondary | | |
| Determine the number and rationale for PTH patients to return to the OR; and    Determine the number of blood transfusions and estimated blood loss and      Determine the recurrence of PTH after TXA, saline, or return to the OR. | Collection number participants and surveys on ENT surgeons’ decision to go to the OR    Collection of electronic health record data on number of blood transfusions and estimated blood loss    Survey families to determine PTH recurred seven days from randomization. | To evaluate if return to the OR can be an outcome for the main trial.    To evaluate if TXA decreased severity of PTH bleeding.      To evaluate if TXA or return to OR prevented PTH recurrence. |
| Tertiary/Exploratory | | |

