# 4 Study Design

## 4.1 Overall Design

Our overall hypothesis for the phase 3 trial is that nebulized TXA will decrease the severity of bleeding and the need for repeat surgical intervention for PTH. To test this hypothesis, we first propose to conduct a multi-center, randomized controlled, blinded pilot trial (phase 2) to assess the feasibility, safety, and the local and systematic absorption of nebulized TXA in children with PTH. Safety and pharmacokinetic data are well known for topical and intravenous administration of TXA but there is limited data on nebulized delivery of TXA. Participants will be randomized at the time of the consent in the emergency department. Earlier PECARN studies experience suggest that pre-consenting patients in surgical clinic will not improve participant enrollment or completion. Children 2 to 17 years old presenting to the ED with PTH will be randomized in a 1:1 ratio to three doses TXA or placebo (saline).  All interventions will be blinded by the investigator, treating clinical care team, and research staff. Only the pharmacist and biostatistician will know the randomization schedule. We will not unblind patients as there is no reversal agent. Clinical teams will be asked to assume the patient received TXA. Patients will be followed during their hospital course and outcomes will be evaluated at seven +/- 1 days after randomization. As this is a pilot study, no stratification or interim analysis will be performed.

[figure not shown]

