# 6 Study Intervention

## 6.1 Study Intervention(s) Administration

### 6.1.1 Study Intervention Description

The intervention will not interfere with or supersede standard ED care for post-tonsillectomy hemorrhage. After determination of eligibility and obtaining informed consent, patients will be randomized to receive nebulized TXA or saline. The only change to ED PTH management is the addition of nebulized study drug. This randomized pilot trial will thus evaluate the feasibility to enroll patients into a trial that will determine the efficacy of nebulized TXA (investigational drug) compared to nebulized normal saline (placebo) to prevent repeat surgical intervention.

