## 8.2.4 FOLLOW UP DATA COLLECTION

**The secondary outcome** (the need for return to the OR for surgical management of PTH) will be followed for up to seven days after randomization.

**Patient-related outcomes measures (PROM)** include pain (as measured by age-appropriate pain scale) and parental/patient anxiety (measured at 7 days after randomization).  The rationale for measuring parent and child anxiety and pain have been documented as measures that significantly predict overall parent satisfaction with perioperative care^28^. To assess patient and parent-centered outcomes of parental and child anxiety we will assess the following scores at day 7 +/- 1-day post-study drug randomization.

1. PROMIS Short Form v1.0 - Anxiety - 8a 31 May2019, PROMIS Early Childhood Parent Report SF v1.0 - Anxiety 8a - 4-1-2021, and Numeric Rating Scale for Anxiety (NRS-A)
2. Wong-Baker Age-appropriate Pain Score & FLACC Behavioral Assessment Scale

For discharged patients, parents will be contacted by a HIPAA compliant text messaging (e.g., TigerConnect App) or phone call for these assessments and communication. If the patient is still in the hospital, research staff may conduct these follow-ups in person.

Wong-Baker FACES® Pain Score:

[figure not shown]

 FLACC Behavioral Pain Assessment Scale

**Parental and child state and trait anxiety**: To assess anxiety in both parents and pediatric participants, we will use validated Patient-Reported Outcomes Measurement Information System (PROMIS) instruments and a Numeric Rating Scale for Anxiety (NRS-A).

1. PROMIS Anxiety Measures

Older children, adolescents, and parents: Anxiety will be measured using the PROMIS Short Form v1.0 – Anxiety – 8a (31 May 2019). This is an 8-item self-report instrument designed to assess symptoms of fear, worry, hyperarousal, and somatic anxiety over the past 7 days. Items are scored on a 5-point Likert scale (Never to Always). Raw scores are converted to standardized T-scores (mean 50, SD 10), allowing comparison to the U.S. general population. Higher T-scores indicate greater anxiety severity.

Young children (early childhood): For children aged 4–7 years, anxiety will be assessed using the PROMIS Early Childhood Parent Report Short Form v1.0 – Anxiety 8a (April 1, 2021). This parent-reported instrument captures observable anxiety-related behaviors and symptoms in young children. It includes 8 items scored on a 5-point response scale and similarly generates standardized T-scores.

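### The recurrence objective treats return to the OR as a condition beside TXA and saline, but it is an unassigned post-randomization event in both arms, so the trial cannot show that it prevented recurrence

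*Protocol*

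**What the plan says.** The Synopsis (Protocol 1.1) sets as a secondary objective "Determine the recurrence of PTH after TXA, saline or return to the OR". The table in Section 3 repeats this, gives the endpoint as "Survey families to determine PTH recurred seven days from randomization", and gives the reason as "To evaluate if TXA or return to OR prevented PTH recurrence". A footnote to the Schedule of Activities (Section 1.3) adds "At seven days, further, evaluate if participants had been readmitted for bleeding after an intervention".

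The rest of the protocol describes a two-arm trial. Section 4.1 randomizes 1:1 to TXA or saline. Section 9.3 defines two analysis populations, those who received TXA and those who received saline. OR return is not assigned: Section 6.1.1 says "The intervention will not interfere with or supersede standard ED care for post-tonsillectomy hemorrhage", and Sections 8.1 and 8.2.2 treat the decision and its reasons as the ENT surgeon's, to be surveyed. Sections 8.1 and 8.2.4 make OR return a secondary outcome, and the latter follows it for up to seven days from randomization.

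On strength of inference, Section 8.1 says the study is not powered for secondary outcomes, and Section 9.4.1 says outcomes are analyzed descriptively.

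**The concern.** In the Section 3 table, return to the OR plays two roles that do not fit together. One secondary row asks whether it can serve as an outcome for the main trial. Another treats it as something that may have prevented an outcome. The second role needs a group of children assigned to OR return, or at least a group separable from the two arms. Neither exists.

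The three labels overlap. A child given TXA and then cauterized falls under both TXA and OR return. A child who rebleeds on Day 3 and is then operated on is a recurrence after study drug and also a member of the OR group, so that group can be defined by the very outcome it is meant to prevent. The clocks differ as well: recurrence is counted from randomization, and a child operated on at Day 5 has about two days of the seven-day window left.

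At stake is one conclusion. If recurrence is tabulated under the three labels and read as the justification invites, the pilot would report something about the preventive value of OR return that its design cannot support.

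**Working it through.** The protocol gives no rate, sample size or power for recurrence, so there is no stated figure to reproduce. Two questions can be checked: how far the three labels overlap, and whether a three-way reading can mislead.

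**1. Overlap.** Inputs: 12 children, 6 per arm (Section 5.5); 22 children, taken as 11 per arm (Section 9.2); the ceiling of 30, taken as 15 per arm (Synopsis). OR rates: 76% without and 61% with TXA (Section 9.2). For a range: the sites' existing rates of 63% to 73% (Section 5.5), applied to both arms, and the cited retrospective cohort's 60.2% and 36.1% (Section 2.2).

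Expected children without OR return = children per arm × (1 − OR rate). At the planning rates:

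- N = 12: saline 6 × 0.24 = 1.4; TXA 6 × 0.39 = 2.3; in the OR 4.6 + 3.7 = 8.2 (unrounded 4.56 + 3.66 = 8.22)
- N = 22: saline 11 × 0.24 = 2.6; TXA 11 × 0.39 = 4.3; in the OR 8.4 + 6.7 = 15.1

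| OR rates, saline / TXA | Without OR, N = 12 (saline / TXA) | N = 22 | N = 30 |
|---|---|---|---|
| 76% / 61% | 1.4 / 2.3 | 2.6 / 4.3 | 3.6 / 5.9 |
| 73% / 73% | 1.6 / 1.6 | 3.0 / 3.0 | 4.1 / 4.1 |
| 63% / 63% | 2.2 / 2.2 | 4.1 / 4.1 | 5.5 / 5.5 |
| 60.2% / 36.1% | 2.4 / 3.8 | 4.4 / 7.0 | 6.0 / 9.6 |

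At 76%, the chance that the 12-child study has at most one saline child without OR return is 0.76^6 + 6 × 0.24 × 0.76^5 = 0.19 + 0.37 = 0.56. At the planning rates, the OR group would be 0.76 / (0.76 + 0.61) = 55% saline and 45% TXA. It is a mixture of the two arms.

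**2. Direction of a possible bias, under assumptions.** None of these figures is in the protocol. Suppose half the children bleed severely; recurrence is 20% in them and 8% in the rest; neither TXA nor OR return affects recurrence; OR rates are 96% (saline) and 81% (TXA) in severe cases and 56% and 41% in the others, which average to 76% and 61%. Then recurrence is:

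- OR group: [(0.96 + 0.81) × 0.20 + (0.56 + 0.41) × 0.08] / 2.74 = 0.4316 / 2.74 = 15.8%
- TXA without OR: (0.19 × 0.20 + 0.59 × 0.08) / 0.78 = 10.9%
- Saline without OR: (0.04 × 0.20 + 0.44 × 0.08) / 0.48 = 9.0%
- Each randomized arm: 0.5 × 0.20 + 0.5 × 0.08 = 14.0%

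The three labels differ although nothing has an effect. The randomized arms agree, as they should.

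**3. The Day 7 ± 1 contact.** A contact on Day 6 cannot by itself report a Day 7 bleed. Assume a constant rate over seven days and recurrence between 4.9% (TXA group of the cited cohort, Section 2.2) and 14.3% (after operation, Section 2.3.2). If every child were contacted on Day 6, the expected number missed is N × p / 7: 0.08 to 0.25 in 12 children, and 22 × 0.049 / 7 = 0.15 to 22 × 0.143 / 7 = 0.45 in 22.

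**The case against.** The strongest reply is that the objective only says recurrence will be determined, which is descriptive. No analysis section forms an OR group, no text moves TXA children into one, and no test of three conditions is specified. How recurrence is tabulated around OR return is commonly left to a statistical analysis plan. All of this stands, and it limits the weight of the point. It does not rescue the justification, which is causal and is fixed in the protocol: describing the data does not make OR return a preventive treatment that the trial evaluated.

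Three stronger readings are tempting and are not supported.

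- A reader might infer that a surgery-versus-TXA result would steer phase 3. In Sections 4.1 and 9.2 the need for surgery is the phase 3 outcome, not a comparator, and the go/no-go threshold is enrollment.
- A reader might take it as given that surgeons operate on the worst bleeders. The protocol does not say so, and it surveys surgeons to learn their reasons. Confounding by severity is plausible but is an assumption.
- A reader might infer that the Day 7 ± 1 window makes a seven-day outcome impossible to ascertain. Adverse events are recorded to Day 30 ± 5, and deterioration at any time counts as one (Sections 8.3.4 and 8.3.5). Section 4.4 follows surgical control for 7 to 30 days, and Section 7.3 includes additional bleeding over that period. What remains is that the Day 30 column in Section 1.3 lists only adverse events, with no recurrence item.

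**Conclusion.** The point holds for the wording of the recurrence objective and its justification. OR return is an unassigned, post-randomization outcome that occurs in both arms. It is not a third condition, and the trial cannot show that it prevented recurrence. That follows from the design alone and needs no assumption about severity.

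The overlap is large: at the planning rates, about 8 of 12 or 15 of 22 children would fall under OR return as well as under their arm. These counts depend on the assumed OR rates. At the cited cohort's lower rates more children avoid the OR, but the overlap remains.

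The consequence is modest. Recurrence by randomized arm is a valid comparison, although 6 versus 6 or 11 versus 11 children support description only. The harm is confined to one unsupported conclusion. The correction is still worth making, because it costs almost nothing and changes what the trial may claim. The Day 6 issue is minor: under half an expected event in 22 children, before any recovery through adverse event reporting.

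**What to change.** In the Synopsis and in Section 3, restate the objective as recurrence of PTH within seven days of randomization, described by randomized arm (TXA or saline), whether or not the child went to the OR. Report recurrence after an OR procedure only as a description within each arm, timed from the procedure. Delete from the justification the claim that return to the OR prevented recurrence. Use the same definition in both places and in the Section 1.3 footnote, which at present speaks of readmission for bleeding after an intervention.

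As a small addition, record the date of any rebleed and, for a child contacted on Day 6, confirm Day 7 status at the Day 30 contact already planned.

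The cost is the rewording of one objective row, its Synopsis counterpart and one footnote, plus one question on an existing call. Arms, visits and clinical care do not change. The trial gives up an informal comparison with OR return that its design cannot support.

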# 4 Study Design

## 4.1 Overall Design

Our overall hypothesis for the phase 3 trial is that nebulized TXA will decrease the severity of bleeding and the need for repeat surgical intervention for PTH. To test this hypothesis, we first propose to conduct a multi-center, randomized controlled, blinded pilot trial (phase 2) to assess the feasibility, safety, and the local and systematic absorption of nebulized TXA in children with PTH. Safety and pharmacokinetic data are well known for topical and intravenous administration of TXA but there is limited data on nebulized delivery of TXA. Participants will be randomized at the time of the consent in the emergency department. Earlier PECARN studies experience suggest that pre-consenting patients in surgical clinic will not improve participant enrollment or completion. Children 2 to 17 years old presenting to the ED with PTH will be randomized in a 1:1 ratio to three doses TXA or placebo (saline).  All interventions will be blinded by the investigator, treating clinical care team, and research staff. Only the pharmacist and biostatistician will know the randomization schedule. We will not unblind patients as there is no reversal agent. Clinical teams will be asked to assume the patient received TXA. Patients will be followed during their hospital course and outcomes will be evaluated at seven +/- 1 days after randomization. As this is a pilot study, no stratification or interim analysis will be performed.

[figure not shown]

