## 5.5 Strategies for Recruitment and Retention

The pilot study aims to test the feasibility of enrolling 0.6 patients per site per month. The specific goal for this pilot trial is to enroll 12 patients (6 treatment groups & 6 control group) at the University of Texas Health Science Center (UTHSCSA)/University Hospital in San Antonio, TX. The participants will be children who present to the emergency department (ED) with secondary posttonsillectomy hemorrhage (PTH) occurring 24 hours or more after their tonsillectomy. PTH patients will be screened and approached in the ED. Participants will be followed as outpatients for one week post-randomization. Due to the short follow-up period, we do not expect a significant loss of participants. However, text, phone, and e-mail information will be obtained from each participant to give the study team multiple options for gathering data on secondary and tertiary objectives. In this pilot analysis, we will offer participants an incentive to complete all study procedures. We will also closely monitor study completion to determine if participant incentives are necessary for the main trial. This pilot study will help assess the feasibility of enrollment rates and the effectiveness of follow up methods, which will inform the design and implementation of the larger main trial.

The investigators will enroll at the University of Texas Health Science Center (UTHSCSA)/University Hospital in San Antonio, TX for the single site and the multi-site study, the University of California at Davis Medical Center in Davis, CA, and Hasbro Children’s Hospital in Providence, RI. Each of the ENT and ED colleagues at each site have provided the incidence of PTH, percentage that return to the OR, and the monthly ED visit rate. Previous studies document that PTH primarily presents at night, therefore we arrange for 24/7 coverage at each site.

| **Site** | **Annual PTH Incidence** | **Going to OR** | **Monthly ED Visits** |
| --- | --- | --- | --- |
| San Antonio, TX | 5.4% | 73% | 1.60 |
| Davis, CA | 3.2% | 70% | 0.63 |
| Providence, RI | 2.8% | 63% | 2.80 |

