## 6.3 Measures to Minimize Bias: Randomization and Blinding

Due to the narrow time window of study intervention, randomization must not delay treatment. To complete the randomization quickly, the study intervention will be preassigned using a central randomization process. Prior to enrollment at each site, a study drug box having two vials (1000 mg per vial) of blinded study drug with a numeric identification code corresponding to the treatment assignment will be designated as the “Use Next Box." All interventions will be blinded to the investigator, clinical care team, and research staff. Only the pharmacist and biostatistician will know the randomization schedule. Unblinding is not allowed. Clinicians will be instructed to assume that the patient has received TXA and treat accordingly.

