# 9 Statistical Considerations

## 9.1 Statistical Hypotheses

The pilot study is not designed to test an efficacy hypothesis, but rather to determine the feasibility for patient enrollment and the number of doses received per patient.

**Our primary hypothesis** for the single site and the multi-site study is that we can enroll at least 0.6 patients per site per month and deliver a minimum of two out of three planned nebulized TXA doses to >90% of enrolled patients.  The single site study will only be one year and the multi-site study for 18 months. We will test each of this (yes/no) hypothesis using a Mantel Haenszel test stratified by site for a total of 12 patients for the single-site study for greater than 24 nebulization and for the multi-site study up to 22 patients with greater than 44 nebulization's recorded as delivered.

**Our secondary goals** will be to determine if nebulized TXA prevents going to the OR for PTH and utilization of blood products. These goals are not powered to be tested in the pilot study. **Our second aim** is to verify a pulmonary physiological based pharmacokinetic (PBPK) model (i.e., nasal cavity, pharynx, and lungs) will predict the change in the area under the curve (AUC0-α) of TXA concentration in systemic compartments with accuracy (average absolute fold error <2) and precision (average fold error <2). We will calculate the AUC of accuracy and precision of the model using the linear trapezoid rule. For the PBPK model, we will use previously published PK data to construct the model before verifying it with systematic samples.

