### 9.4.2 Analysis of the Primary Efficacy Endpoint(s)

Differences between TXA and saline conditions with respect to the primary outcome (i.e., need for surgical intervention: yes or no) will be analyzed statistically using the Mantel Haenszel test stratified by site.

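### Section 4.1 rules out stratification, yet 9.4.2 compares arms by site and 5.5 sets 6 and 6 with no stated mechanism; small blocked lists per site are a cheap, optional improvement

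*Protocol*

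**What the plan says.** - Section 4.1 sets 1:1 allocation to TXA or saline and then states: "As this is a pilot study, no stratification or interim analysis will be performed". It does not say whether this concerns the randomization, the analysis or both.
- Section 6.3 says that "the study intervention will be preassigned using a central randomization process" and that numbered boxes are made ready before enrolment at each site ("Prior to enrollment at each site, a study drug box having two vials"). Neither 6.2.4 nor 6.3 mentions blocking or balance within site.
- Section 9.4.2 says that the difference between TXA and saline in need for surgery "will be analyzed statistically using the Mantel Haenszel test stratified by site".
- Section 5.5 gives the single-site goal as "enroll 12 patients (6 treatment groups & 6 control group) at the University of Texas Health Science Center".
- Section 9.2 sets the multi-site target at 22 patients over 3 sites and 12 months, with no split by arm or site.
- Section 9.4.1 calls the feasibility, efficacy and safety analyses descriptive.

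**The concern.** The analysis conditions on a factor that the design says it will not balance. A Mantel-Haenszel test compares TXA with saline within each site, so a site needs children in both arms to contribute. The site table in Section 5.5 shows unequal volumes, from 0.63 to 2.80 monthly ED visits, so one of the three sites may enrol very few children. If they all receive the same treatment, their outcomes drop out of the test.

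The single-site stage raises a separate question. It has one stratum, so the small-site problem cannot arise there. But the split of 6 and 6 is stated as a goal, and an unblocked 1:1 list would often miss it. Only TXA children yield concentrations for verifying the PBPK model, and TXA concentration is among the primary objectives in Section 3. The number of usable samples would then depend on chance.

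**Working it through.** **Target reproduced.** Section 9.2: 0.6 × 3 × 12 = 21.6, rounded up to 22. Per site this is 0.6 × 12 = 7.2, or about 7.

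**Why a one-arm site drops out.** Take a site with N children, n₁ on TXA, n₀ on saline, m operations in total and a among TXA children. The site contributes a − n₁m/N to the numerator and n₁n₀m(N − m)/[N²(N − 1)] to the variance. If n₀ = 0, then n₁ = N and a = m, so both terms are 0. The same holds if n₁ = 0.

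**Size of the sites.** Assume enrolment proportional to the monthly ED visits in Section 5.5 (1.60, 0.63, 2.80; sum 5.03):
- San Antonio: 22 × 1.60/5.03 = 7.0
- Davis: 22 × 0.63/5.03 = 2.8
- Providence: 22 × 2.80/5.03 = 12.2

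**Chance that a site of n children has one arm only.** Simple 1:1 randomization: 2 × 0.5ⁿ. One central list forced to 11:11 over all sites: 2 × C(22 − n, 11 − n)/C(22, 11).

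| n | Simple | Central 11:11 |
|---|---|---|
| 2 | 50% | 48% |
| 3 | 25% | 21% |
| 4 | 12.5% | 9.0% |
| 7 | 1.6% | 0.4% |
| 12 | 0.05% | 0% |

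The planned rate puts the smallest site at n of about 7, which would need 0.6/0.63 = 95% of its monthly visits. Half of its 0.63 × 12 = 7.6 yearly visits gives about 4. Proportional enrolment of 22 gives about 3; of the synopsis maximum of 30, it gives 30 × 0.63/5.03 = 3.8, or about 4.

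These figures hold the site size fixed. In a simulation of 200,000 trials with random site sizes (multinomial in the same proportions, simple randomization), the smallest site was empty or one-arm in 43%. In 22% of trials it had 0 or 1 child, which no list can repair.

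**Expected loss.** With fixed sizes of 7, 3 and 12 under simple randomization: 7 × 0.0156 + 3 × 0.25 + 12 × 0.0005 = 0.87 patients. The simulation gives 0.90 of 22.

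**Single-site stage, if allocation is simple 1:1.**
- P(exactly 6:6) = C(12, 6)/2¹² = 924/4096 = 22.6%.
- P(at most 4 TXA) = (1 + 12 + 66 + 220 + 495)/4096 = 794/4096 = 19.4%.

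Two samples per child make at most 8 TXA samples in that case, against 12 with 6 TXA children. Section 9.4.3 accepts the model if 90% of observed concentrations lie in the prediction interval. One value outside gives 7/8 = 87.5% (fails) with 8 samples, but 11/12 = 91.7% (passes) with 12.

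**With blocks within site.** In blocks of 2 or 4, a site with 3 or more children cannot be one-arm. A site with 2 children is one-arm with probability 0 (blocks of 2) or 2/C(4, 2) = 33% (blocks of 4).

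**The case against.** The protocol never states simple randomization. Ruling out stratification does not rule out blocking, a goal of 6 and 6 fits a balanced list of 12, and boxes held at each site could come from site-specific lists. Block details are often left to a randomization plan. This stands: the 23% and 19% are conditional on simple allocation.

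At the protocol's own planning rate the small-site risk is 1.6% per site. The pilot is unpowered and its analyses are descriptive. Sections 2.2 and 4.2 say that few samples suffice for the PBPK model, and no minimum number of TXA children is set. This also stands and lowers the priority. Against the planning rate, Section 3 itself expects numbers per site to differ widely, and 0.6 per month would need nearly every visit at the smallest site.

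Three stronger readings are tempting and are not supported:
- A reader might infer that the stratified test is invalid after unstratified randomization. It is not; the cost is lost information.
- A reader might link the 6:6 goal to the risk of a one-arm site. The goal belongs to the 12-patient single-site stage; the risk exists only in the three-site stage.
- A reader might count Section 9.1 as further evidence, since it too names a Mantel-Haenszel test stratified by site. It applies that test to enrolment and doses delivered, which are not comparisons between arms, so balance between arms has no bearing on it.

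**Conclusion.** The point holds in limited form. Section 4.1 rules out stratification, 9.4.2 relies on comparison within site, 5.5 sets 6 and 6, and no stated mechanism secures balance at either stage.

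- **Multi-site stage:** the chance that the smallest site is one-arm runs from 1.6% (about 7 children) to 25% (about 3 children, given proportional enrolment and simple randomization; 21% under a central 11:11 list). The average loss under proportional enrolment and simple randomization is about 0.9 of 22 patients, and the test remains valid.
- **Single-site stage:** if allocation is simple, 6:6 is missed about 77% of the time and at most 4 TXA children are enrolled 19% of the time. A blocked list would avoid this.

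Given a descriptive, unpowered pilot, this is an optional, low-cost improvement.

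**What to change.** In Section 4.1, replace only the words on stratification and keep the statement that no interim analysis is planned. Suggested text: *Allocation will be 1:1 in permuted blocks generated separately for each site, in small blocks (2 or 4) not disclosed to sites, with block boundaries completing at 12 in the single-site stage. No interim analysis will be performed.* Keep the site-stratified analysis in 9.4.2.

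The cost is one list per site; boxes are already prepared in advance for each site. The downsides are modest:
- Assignments become slightly more predictable if the blind fails.
- A site with 2 children can still be one-arm (33%) with blocks of 4.
- Replacement of randomized patients, allowed in Section 7.2, can disturb an exact 6:6.
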